##### Co-primary outcome: unplanned healthcare utilization

Unplanned healthcare utilization related to surgery within 30 days of ureteroscopy, defined as a hierarchical composite rank score components in decreasing rank order as described in the protocol. The composite endpoint will be nonparametrically assessed by comparing global composite rank score outcomes [34] across pairs of participants and evaluating a win ratio using the Mann–Whitney *U* statistic. The win proportion is the probability that a stent omission participant experiences better outcomes when compared to a participant with stent, thus representing the effect size.

#### Randomized cohort analysis

The analysis of the hierarchical composite endpoint of healthcare utilization using the Win Ratio [29] in the RCT will use the ITT population and will use the unmatched approach [35, 36]. The composite healthcare utilization metric within 30 days will be an assigned score for each patient based upon the highest ureteroscopy-related utilization level that they participate in with levels defined in decreasing order: (6) Hospitalization and ICU care; (5) unplanned hospitalization; (4) unplanned additional operating room or interventional radiology procedure; (3) emergency department (ED) visit; (2) ambulatory encounter: clinic visit; and (1) number of ambulatory patient/provider interactions. Then the rank of each patient in the stent omission arm will be compared to each patient in the stent arm using the unplanned healthcare utilization ranking rules described above such that each pair will have a winner. Summary statistics for the hierarchical composite win ratio endpoint will be presented, including the number of total pairs, and number and proportion of pairs that favor stent omission for each component of the unplanned healthcare utilization outcome. The number of winners and losers for stent omission and corresponding win ratio will be reported with the 97.5% (bootstrapped-based) confidence interval and *p*-value based on the Chi-square statistic. In addition, the probability of a participant with stent omission doing better than a participant with a stent will be presented. It is not expected to have missing data for this endpoint but if there is then multiple imputation will be used. Sensitivity analysis will be conducted with the same analysis in the healthcare utilization modified intent-to-treat (HCUmITT, see Sect. 20c) population to assess the robustness of the effect found in the primary analysis.

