### Sample size {14}

The sample size was derived by the sample needed to power each co-primary endpoint for the RCT cohort. The larger sample size among the co-primary endpoints was used to estimate the final RCT cohort size. Each power calculation used a two-sided significance level of 2.5% to allow for two primary endpoints for a trial-level type I error of 5% as described below.

Postoperative days 7–10 PROMIS® Pain Interference change from pre-surgery is a co-primary endpoint; 101 participants per treatment arm will provide the RCT cohort with at least 90% power to detect a mean difference between stent placement vs. omission treatment groups of 5 points with an assumed standard deviation (SD) of 10 points, based on a two-sample *t* test (SAS 9.4), with a two-sided significance level of 2.5%. Previous work estimated that a clinically meaningful difference in PROMIS® Pain Interference is 2–6 points [25, 26]. A pilot study at our institution found an initial difference between stent omission and placement of 7.2 points with a SD of 13 for change and a SD of 10 at each time point. We expect our pilot may overestimate the treatment effect. Thus, we have targeted a difference of 5 points to represent a clinically significant target. A 10% loss to follow-up (failure to respond to the 7–10-day questionnaire) is assumed. Thus, 112 patients are needed per arm (total 224 patients). After consent, we estimate that 15% of patients who plan to be randomized will be unable to do so owing to intra-surgical factors that deem the procedure as complicated requiring 264 patients consented to the randomization cohort to attain 224 randomized patients.

Unplanned healthcare utilization within 30 days of ureteroscopy is the second co-primary endpoint.

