With a modest probability of improvement in the reduction of healthcare utilization in ureteroscopy with stent omission, the impact in morbidity reduction and cost reduction would be great. There are no current estimates in the literature that help inform a minimum important difference for the win ratio estimate of healthcare utilization, our co-primary endpoint. So, we reasoned that a marginal probabilistic index, which is the effect size measure corresponding to the nonparametric Mann–Whitney *U* statistic that is used to test the hierarchical composite “win ratio” endpoint [27], of at least 67%, would be impactful as the study could conclude that a randomly chosen participant with stent omission has a two-thirds or greater probability of lower healthcare utilization than a randomly chosen participant treated with a stent. In the RCT with a two-sided 2.5% alpha and requiring 90% power to detect a treatment effect of 67%, 72 patients would be required per treatment arm. The sample size is based on the Finkelstein and Schoenfeld methods [28] for analysis of hierarchical composite endpoints, later called the win ratio by Pocock et al. based on the nonparametric Mann–Whitney *U* statistic [29]; the formula is provided in Yosef et al. [30].

The observational cohort sample size was derived from an assumption that 1/3 of patients approached and consented would be willing to be randomized. Thus, the observational cohort will consist of the estimated 2/3 (528) of patients who are approached and decline the RCT. With those assumptions, we find the following power for each primary endpoint.

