## Assignment of interventions: allocation

### Sequence generation {16a}

Participants in the randomization cohort will be randomized intraoperatively using an online computer-based system (https://randomize.net/) to either stent omission or stent placement in a 1:1 ratio. This will take place after the completion of the lithotripsy portion of the procedure and verification of second-stage eligibility by the operating urologist. Blocked, stratified randomization based upon surgeon-classified stone location (renal only versus ureteral with or without renal), with random block sizes will be used to ensure group balance.

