#### Randomized cohort analysis

A linear (ANCOVA) model will be used on the intention to treat (ITT) population to compare the two treatments, with PROMIS Pain Interference *t*-score at postoperative days 7–10 as the dependent variable and treatment group, stratification factor (stone location [kidney or ureter]) and pre-surgery (baseline) Pain Interference *t*-score as the independent variables [33]. The adjusted parameter estimate for treatment group (stent omission vs. placement) will be reported with the associated 97.5% CI and *p*-value (based on a type 3 *F*-test) that allows testing the hypothesis that Pain Interference differs between the two treatment groups. Multiple imputation will be used to address missing data and will be described fully in the statistical analysis plan. Sensitivity analysis will be conducted with the same analysis in the pain-modified intent-to-treat (PmITT, see Sect. 20c) population to assess the robustness of the effect found in the primary analysis. Additional sensitivity analysis will be conducted if there is baseline imbalance.

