#### Observational cohort analysis

The same general approach used in the RCT will be applied to the observational study with the healthcare utilization rank for each patient and the rules for comparing pairs of patients between arms. However, to address possible clustering among surgeons and sites while protecting unbiasedness of treatment effects and to preserve power, the analysis approach of Dong et al. [36] will be implemented. Specifically, this approach incorporates the notion of risk-matching by forming strata according to risk groups (as described by Pocock et al. [29]) without resulting in loss of information by losing matched pairs when there is an imbalance in sample size between groups. The stratified approach uses the unmatched method to calculate the win ratio statistics within stratum, thus providing an intermediate position between the matched pairs approach and the unmatched approach. Specifically, we will include site in the determination of risk strata. To form risk group strata, the outcome of healthcare utilization categorized as yes versus no will be modeled using a logistic model with fixed effects including baseline variables: site, stone location (kidney only vs ureter), stone size, and Charlson comorbidity score. A risk score for each patient will be obtained using the logistic model’s coefficients. Stratification will be performed based upon risk score. Risk score groups will be defined using natural bins (if they are apparent) or percentiles. Then, within each stratum, an unmatched approach will be used to calculate the win ratio. The overall win ratio will be estimated using the Mantel–Haenszel-type weight and reported with a 97.5% confidence interval. The method for adjustment will be described in detail in the SAP and finalized prior to data lock. Sensitivity analysis will be conducted with the same analysis in the HCUmITT population to assess the robustness of the effect found in the primary analysis.

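### The randomized utilization co-primary uses an unstratified win ratio although randomization is stratified by stone location; if location is prognostic the test is somewhat conservative, with little effect on power at the design effect

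*Protocol article*

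**What the plan says.** - **Randomization** (Sequence generation {16a}): "Blocked, stratified randomization based upon surgeon-classified stone location (renal only versus ureteral with or without renal"). No other stratification factor is named.
- **Utilization co-primary, randomized cohort** (Statistical methods {20a}): the hierarchical composite "in the RCT will use the ITT population and will use the unmatched approach". Each omission patient's rank is compared with each stent patient's rank. Neither a stratum nor stone location is mentioned.
- **Pain co-primary, randomized cohort**: the ANCOVA has as independent variables "treatment group, stratification factor (stone location [kidney or ureter"]) and the baseline score.
- **Secondary utilization outcomes, randomized cohort**: the models for the separate components of the same composite also include stone location as the stratification factor.
- **Utilization co-primary, observational cohort**: "The stratified approach uses the unmatched method to calculate the win ratio statistics within stratum", with Mantel–Haenszel-type weights to combine strata. The strata come from a risk score that includes stone location.
- **Subgroup analyses {20b}**: a separate win ratio is planned for each stone location.

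**The concern.** Blocking within stone location prevents the arms from differing by chance in their mix of renal and ureteral cases. The usual variance of an all-pairs Mann–Whitney statistic still allows for that chance difference. If location is prognostic, the stated variance is therefore larger than the true one, the test rejects less often than its nominal level, and some power is lost. A bootstrap that ignores strata would be expected to widen the confidence interval for the same reason.

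The choice also sits oddly with the rest of the plan. The other co-primary and the component models follow the randomization, and the stratified win ratio is already specified a section later. That later section describes it as lying between the matched and unmatched approaches, so in the protocol's own terms the unmatched analysis of the randomized cohort is not a stratified one.

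**Working it through.** **Inputs from the protocol** (Sample size {14}). Alpha: "Each power calculation used a two-sided significance level of 2.5% to allow for two primary endpoints". Target: "requiring 90% power to detect a treatment effect of 67%, 72 patients would be required per treatment arm". The index is marginal, "which is the effect size measure corresponding to the nonparametric Mann–Whitney *U* statistic". Planned size, set by the pain endpoint: "Thus, 112 patients are needed per arm (total 224 patients"). No missing utilization data are expected.

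**Step 1: reproduce the plan's figure.** Noether's formula for the total with 1:1 allocation:

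N = (z₀.₉₈₇₅ + z₀.₉₀)² / [12 × 0.5 × 0.5 × (0.67 − 0.5)²] = (2.2414 + 1.2816)² / (3 × 0.0289) = 143.2, so 72 per arm. This matches.

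**Step 2: unstratified power at the planned size.** Power = Φ(|p − 0.5| × √(3N) − 2.2414), with N = 224 and √672 = 25.923:

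- p = 0.67: Φ(4.407 − 2.241) = 98.5%
- p = 0.64: Φ(3.629 − 2.241) = 91.7%
- p = 0.62: Φ(3.111 − 2.241) = 80.8%

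**Step 3: what stratifying changes.** The protocol does not say how strongly location predicts utilization, so this was varied. It is expressed as the probability that a patient in one stratum fares worse than a patient in the other. Assumptions: two equal strata, treatment balanced within strata, and a normal latent outcome. The outcome was either kept continuous or cut into levels with ties: 40% no utilization; 15, 10 and 5% with one, two and three contacts; 10% clinic visit; 12% emergency visit; 2% procedure; 5% hospitalization; 1% ICU. The comparison is the unstratified Mann–Whitney test against a two-stratum weighted test, with 112 per arm and 4,000 runs per setting. Cells give unstratified / stratified power in %. The column effect is the latent within-stratum index.

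| Prognosis of location | 0.67, continuous | 0.67, ties | 0.62, continuous | 0.62, ties |
|---|---|---|---|---|
| none (0.50) | 99.1 / 99.0 | 97.0 / 97.0 | 80.5 / 80.3 | 73.9 / 73.7 |
| weak (0.56) | 99.0 / 98.9 | 97.2 / 97.2 | 81.7 / 81.6 | 74.5 / 74.6 |
| moderate (0.64) | 98.4 / 98.7 | 97.6 / 97.8 | 79.5 / 81.3 | 76.0 / 77.6 |
| strong (0.71) | 98.1 / 98.8 | 96.8 / 97.7 | 75.6 / 81.0 | 72.5 / 77.5 |

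With a 20/80 split of strata, effect 0.62 and ties, the results were 74.1 / 74.0 (none), 73.9 / 74.1 (weak) and 74.6 / 75.9 (moderate).

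**Step 4: a logistic variant.** Here a log-odds shift d corresponds to the index e^d(e^d − 1 − d)/(e^d − 1)². Shifts for location of 0.5, 1.0 and 1.5 give 0.58, 0.66 and 0.73.

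- Treatment log-odds ratio −1.05 (index about 0.67; ordinal outcome with assumed level frequencies; 3,000 runs): 95.8 / 95.6 with no prognosis, then 95.3 / 95.5, 95.4 / 96.0 and 92.4 / 94.8.
- Treatment log-odds ratio −0.8 (index about 0.63; 4,000 runs): 77.9 / 78.4, 76.0 / 78.6 and 70.3 / 76.6, which are gains of 0.5, 2.6 and 6.3 points.

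**Step 5: type I error, nominal 2.5%.** Normal model with ties, 10,000 runs: 2.3 / 2.3 (none), 2.2 / 2.7 (moderate), 1.6 / 2.3 (strong). Logistic model, 4,000 runs: 2.0 / 2.1, 2.4 / 2.9 and 1.4 / 2.6 for location shifts 0.5, 1.0 and 1.5. The Monte Carlo standard error at 2.5% is √(0.025 × 0.975 / 10,000) = 0.16 point and √(0.025 × 0.975 / 4,000) = 0.25 point respectively. Only the strong-prognosis results show clear conservatism.

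**The case against.** The strongest reply is that nothing here is invalid and little is lost. The unstratified win ratio is a legitimate intention-to-treat comparison, and it does not inflate false positives. The pain endpoint gives this endpoint 112 per arm where it needs 72, and unstratified power at 0.67 stayed above 90% in every 112-per-arm setting. A visible loss requires both a smaller true effect and a strongly prognostic location, and the documents establish neither. All of that stands.

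A second reply also stands. The protocol defines its effect as a probability over all omission–stent pairs, and the planned analysis estimates exactly that. A stratified win ratio estimates a weighted within-stratum quantity. A reader might infer that stratifying is free, but this change of estimand is a real cost. The efficiency cost is negligible: at most about 0.3 point at 112 per arm.

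Two further replies carry less weight. The by-location win ratios are subgroup analyses and leave the primary test unchanged, although they do mean that location is not ignored altogether. The SAP might add stratification, and both win-ratio sections cite the same methods reference. But the deferral of adjustment to the SAP is written for the observational cohort only; for the randomized cohort the method is stated.

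The 0.67 target is not a secure reason to dismiss smaller effects. The protocol says that no literature estimate informs it, its background reports a trend for stenting to reduce unplanned visits, and its observational power section works with 60.1% to 64.3%.

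**Conclusion.** The point holds as a modest inconsistency. The randomized utilization co-primary does not follow the trial's own randomization stratum, while the other randomized-cohort models do. If location is prognostic, the test is conservative, clearly so only under strong prognosis (1.4 to 1.6% against 2.5%). The wider interval follows by reasoning and was not simulated.

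The power gain from stratifying at 112 per arm is:

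- **At index 0.67:** about 0 to 1 point, up to about 2 under strong prognosis with ties.
- **At about 0.62 to 0.63:** about 0 points with weak, 2 to 3 with moderate and 5 to 6 with strong prognosis.

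A reader might go further and infer that this co-primary is underpowered or its test invalid. The documents do not support that: formula power at the design effect is 98.5%, and the error is on the conservative side. These sizes rest on assumed prognostic strengths, stratum splits and outcome frequencies, none of which the protocol gives.

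**What to change.** In the utilization section for the randomized cohort, make the primary analysis a win ratio stratified by stone location as recorded at randomization: unmatched comparisons within the renal-only and ureteral strata, combined with the Mantel–Haenszel-type weights already specified for the observational cohort, and bootstrap resampling within strata. Report the unstratified win ratio and the marginal win probability as a sensitivity analysis, so that the quantity behind the sample size remains visible.

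The cost is a sentence or two of text, settled before data lock. The primary estimate changes from the marginal index to a weighted within-stratum one, which the text should say. If the marginal estimate is preferred as primary, state the reason for leaving the stratum out.

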#### Observational cohort analysis

The same general approach used in the RCT will be applied to the observational study with the healthcare utilization rank for each patient and the rules for comparing pairs of patients between arms. However, to address possible clustering among surgeons and sites while protecting unbiasedness of treatment effects and to preserve power, the analysis approach of Dong et al. [36] will be implemented. Specifically, this approach incorporates the notion of risk-matching by forming strata according to risk groups (as described by Pocock et al. [29]) without resulting in loss of information by losing matched pairs when there is an imbalance in sample size between groups. The stratified approach uses the unmatched method to calculate the win ratio statistics within stratum, thus providing an intermediate position between the matched pairs approach and the unmatched approach. Specifically, we will include site in the determination of risk strata. To form risk group strata, the outcome of healthcare utilization categorized as yes versus no will be modeled using a logistic model with fixed effects including baseline variables: site, stone location (kidney only vs ureter), stone size, and Charlson comorbidity score. A risk score for each patient will be obtained using the logistic model’s coefficients. Stratification will be performed based upon risk score. Risk score groups will be defined using natural bins (if they are apparent) or percentiles. Then, within each stratum, an unmatched approach will be used to calculate the win ratio. The overall win ratio will be estimated using the Mantel–Haenszel-type weight and reported with a 97.5% confidence interval. The method for adjustment will be described in detail in the SAP and finalized prior to data lock. Sensitivity analysis will be conducted with the same analysis in the HCUmITT population to assess the robustness of the effect found in the primary analysis.

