The power estimates presented assume that each observation is independent. However, due to surgeon preference in the observational cohort, there may be a potential for clustering which could impact the power of the study. We expect that surgeons within a site may behave more similarly and the variability between sites will be the correlation that will be important. The intraclass correlation (ICC) across multiple studies and therapeutic areas has been shown to likely be small, with a range between 0.01 and 0.05 [31]. Using our planned sample sizes, we can estimate the sample size needed under a range of ICCs using a method described by Klar and Donner [32] with an estimate of the sample size inflation factor (IF) based upon the ICC and the average sample size per cluster. Table 3 provides the power from using the effective sample size and the assumed proportions for each arm (stent vs stent omission using standard power calculations for the two-arm mean difference using a *t*-test with a two-sided type I error of 0.025 with the assumptions used for Pain Interference described above.

**Table 3 Tab3:** Power for pain interference co-primary endpoint in observational cohort with clustering effect (ICC), assuming 14 participating sites

Proportion agrees to randomization	Total approached	Final observational cohort sample size	Proportion stented	ICC group			
				**0**	**0.01**	**0.02**	**0.05**
33%	792	404	70%	99.1%	96.5%	92.3%	76.3%
			50%	99.7%	98.6%	96.1%	83.7%
			25%	99.1%	94.4%	89.0%	71.0%
50%	528	202	70%	84.2%	78.6%	73.4%	59.6%
			50%	90.0%	85.8%	81.2%	68.0%
			25%	86.7%	73.5%	68.0%	54.2%

For the co-primary endpoint of healthcare utilization in the observation cohort, if we assume that the stented proportion is 50%, with 202 participants per treatment group and a two-sided 2.5% type I error (alpha), we have 90% power to detect a treatment effect, marginal probabilistic index, of 60.1%. If the stented proportion is as low as 25% or as great as 75%, then we can infer that with 90% power, we will be able to detect a treatment effect between 60.1% and 64.3% as the sample size will be at least 101 per stent group.

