#### Observational cohort analysis

The primary analysis for the observational study will be similar to the model described in the randomized cohort except additional independent patient and surgical baseline covariates (age, sex, body mass index (BMI), Charlson comorbidity index, pre-surgery depression t-score, pre-surgery anxiety *t*-score, narcotic use, stone location (kidney or ureter), and stone size) will be included in the model to adjust for potential confounders that are more likely to be unbalanced between the treatment groups owing to lack of randomization. Additionally, a multivariable model with random effects for physician or practice will be considered if there is further imbalance in these factors.

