##### Secondary outcomes

Analysis of each element of the composite healthcare utilization metric will include separate logistic models for ICU care, unplanned hospitalization, additional unplanned procedure, ED visit, and unplanned clinic visit or testing endpoints. A Poisson model will be used to assess the number of ambulatory patient–provider interactions. The randomized cohort models will include the treatment group and stratification factor (stone location (kidney or ureter)) as independent variables. The observational cohort will include a treatment group and adjust for patient/surgical covariates (age, sex, body mass index (BMI), Charlson comorbidity index, stone location (kidney or ureter), and stone size) as independent variables. These analyses will be performed with the ITT population with a sensitivity analysis using the HCUmITT.

Additional HRQOL endpoints, including PROMIS® Pain Interference scores at 4–6 weeks change from preoperative scores, PROMIS® Pain Intensity *t*-score changes, and NIH LURN SI-10 urinary symptom score changes will be analyzed using ANOVA models as described for the pain interference primary endpoint analysis based upon cohort (RCT or observational). Similarly, ANOVA models will be used to assess ICIQ-S treatment satisfaction scores at postoperative days 7–10 and 4–6 weeks separately. These models will be similar to the primary analysis models based upon cohort for the pain interference primary endpoint except a preoperative score does not apply as satisfaction is only measured after the surgery. Alternatively, if the trajectory of change for the outcome is found to be linear, then a linear mixed model will be used to compare scores at 7 days and 4–6 weeks between treatment arms. The mixed models will add the independent variables of time and the interaction of arm and time, a random effect in the model for patient and an autoregressive covariance matrix. Each analysis will report means with 95% CI at each time for each group, with a model-based type-3 *F*-test comparing treatment groups.

Number of days off work will be described using medians with interquartile ranges by treatment arm in each cohort. Linear models like the treatment satisfaction score models will be used based upon cohort. If the assumptions of the linear model are violated, Poisson models will be used.

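### The risk score behind the observational utilization win ratio has no stent-use term and omits age, sex and BMI, so the ratio may be attenuated where site predicts stenting and may keep residual confounding of either sign

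*Protocol article*

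**What the plan says.** All references are to the protocol article.

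- **Utilization co-primary, Observational cohort analysis.** Utilization (yes or no) is to be "modeled using a logistic model with fixed effects including baseline variables: site, stone location (kidney only vs ureter), stone size, and Charlson comorbidity score". Then, "A risk score for each patient will be obtained using the logistic model’s coefficients". On the strata: "Risk score groups will be defined using natural bins (if they are apparent) or percentiles". An unmatched win ratio is computed within strata and pooled with Mantel–Haenszel-type weights. The approach is chosen to deal with clustering by surgeon and site "while protecting unbiasedness of treatment effects and to preserve power". The section ends its description with "The method for adjustment will be described in detail in the SAP and finalized prior to data lock".
- **Pain co-primary, Observational cohort analysis.** The model has treatment, baseline pain interference, age, sex, BMI, Charlson index, depression, anxiety, narcotic use, stone location and stone size. The added covariates are there "to adjust for potential confounders that are more likely to be unbalanced between the treatment groups owing to lack of randomization". Random effects for physician or practice are only to be considered.
- **Secondary outcomes.** The observational models for each component of the utilization composite include treatment group and "adjust for patient/surgical covariates (age, sex, body mass index (BMI), Charlson comorbidity index, stone location (kidney or ureter), and stone size". Site is not listed.
- **Explanation for the choice of comparators {6b}** leaves stenting in this cohort to the urologist. **Sample size {14}** adds that "due to surgeon preference in the observational cohort, there may be a potential for clustering which could impact the power of the study" and expects surgeons at one site to behave alike.

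**The concern.** There are two separate problems.

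**No stent-use term.** Take two sites with the same patient mix, where site A omits stents more often than site B and omission lowers utilization. A model without stent use gives A a lower-risk coefficient, and part of that is the treatment effect. A patient from A and a patient from B with the same score then do not have the same underlying risk: the patient from A has worse covariates, offset by the site's apparent advantage. Within a score stratum, omission patients come disproportionately from A. They are therefore sicker than the stented patients they are compared with, and the win ratio shrinks toward 1. The trigger is that site, or another score covariate, predicts stenting, which the protocol itself leads one to expect.

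**Missing covariates.** The co-primary composite is adjusted for fewer patient factors than its own component analyses: age, sex and BMI are dropped without a reason.

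At stake are the size of the observational effect estimate and the power to detect it. Both problems also work against the stated aim of an unbiased treatment effect.

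**Working it through.** **1. The plan's own figures.** The Mann–Whitney sample-size formula for equal groups is n per group = (z₀.₉₈₇₅ + z₀.₉₀)² / [6(PI − 0.5)²], where PI is the probabilistic index and (2.241 + 1.282)² = 12.41.
- RCT, PI 0.67: 12.41 / (6 × 0.17²) = 71.6, stated as 72.
- Observational, 202 per group: 0.5 + √(12.41 / 1212) = 0.601, stated as 60.1%.
- Observational, 101 per group: 0.5 + √(12.41 / 606) = 0.643, stated as 64.3%.

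All three reproduce. The planned sample size is not in question.

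**2. Attenuation, true win ratio about 2.0.** From the protocol: 404 patients, 14 sites, about 30% omission. Assumed: five score strata, the outcome distribution, and the between-site SD of the logit of stenting (no site-level stent rates are given). There were 600 simulated cohorts per setting. The percentage lost is 1 − ln(planned) / ln(true-score result).

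| Between-site SD | Stratified on the true score | Score as listed | Log win ratio lost | Score with stent use, set to one value |
|---|---|---|---|---|
| 1.0 | 2.02 | 1.83 | 1 − 0.604/0.703 = 14% | 2.03 |
| 1.5 | 2.00 | 1.72 | 1 − 0.542/0.693 = 22% | 2.04 |
| 2.5 | 2.02 | 1.57 | 1 − 0.451/0.703 = 36% | 2.05 |

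A separate run gave 1.83, 1.72 and 1.56 with the listed score, 1.95–2.02 with a stent-use term, and 1.97 with the listed score when site did not predict stenting. With no treatment effect, both scores gave about 1.0.

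**3. Attenuation, different outcome model, true win ratio about 1.70 (PI about 0.592), 404 patients.** The power column uses z = (PI − 0.5)√(6 × 202) − 2.241, with √1212 = 34.81.

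| Stented share across sites (±1 SD) | Score as listed: win ratio (PI) | With stent-use term | z at the listed-score PI | Power |
|---|---|---|---|---|
| No variation | 1.72 (0.592) | 1.76 | 3.203 − 2.241 = 0.96 | 83% |
| 50–88% | 1.60 (0.580) | 1.73 | 2.785 − 2.241 = 0.54 | 71% |
| 33–96% | 1.49 (0.568) | 1.75 | 2.367 − 2.241 = 0.13 | 55% |
| 18–99% | 1.37 (0.553) | 1.74 | 1.845 − 2.241 = −0.40 | 35% |

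The power column is indicative only. It uses the protocol's 202:202 case, while the simulation has 70% stented, and the formula ignores ties and stratification. Under a null effect the listed score gave 1.00–1.02.

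**4. Omitted confounder.** Same model with 50–88% site variation, plus one unlisted covariate that affects both outcome and stenting (coefficients of 0.3 or 0.5, assumed), 404 patients. Each cell gives the result for a true ratio of 1.0, then for about 1.7.

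| Stented patients' risk, strength | Score as listed | + stent use | + stent use and covariate |
|---|---|---|---|
| Higher, 0.3 | 1.08; 1.70 | 1.10; 1.85 | 1.03; 1.76 |
| Higher, 0.5 | 1.18; 1.86 | 1.21; 2.05 | 1.02; 1.79 |
| Lower, 0.3 | 0.95; 1.49 | 0.94; 1.58 | 1.00; 1.71 |
| Lower, 0.5 | 0.87; 1.34 | 0.85; 1.40 | 0.99; 1.68 |

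The bias takes either sign. In the first row the two problems cancel by chance (1.70), and adding stent use alone moves the estimate away (1.85). Both parts need correcting together.

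**The case against.** **The text is not final.** The covariate list is introduced as non-exhaustive and the adjustment is deferred to the SAP. No sentence excludes a treatment term; its absence is read from a list of baseline variables. This stands as a limit on confidence. It does not remove the point, because the protocol already names the score model's outcome, form and covariates. Elsewhere it says explicitly when treatment belongs in a model.

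**The size is assumed.** Some similarity within sites is expected, but its degree is not given. This stands. The largest SDs describe near-polarised sites, and with no site variation the attenuation all but disappears.

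**The covariate comparison is partly one-sided.** Depression, anxiety, narcotic use and baseline pain interference belong to the pain model. The utilization component models leave them out too, so their absence here is consistent with the other utilization analyses. The score also includes site, which the component models do not list. What remains inconsistent is age, sex and BMI.

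**Stronger readings that the documents do not support.** A reader might infer that the planned win ratio is always biased toward no effect; the net direction is open, as step 4 shows. A reader might speak of known confounding; the protocol calls these factors potential confounders. A reader might expect the observational result to contradict the RCT; every attenuated ratio in steps 2 and 3 stays above 1, the RCT uses a separate unmatched analysis, and comparing the cohorts is only an exploratory objective.

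**Conclusion.** The point holds in a conditional form. As listed, the score is fitted to the outcome in both groups together, with site and without stent use. If site predicts stenting and omission works, the win ratio is pulled toward 1: from about 2.0 to roughly 1.8, 1.7 and 1.6 at assumed between-site SDs of 1.0, 1.5 and 2.5. This mechanism produces no false effect under the null and almost no loss if stenting does not vary by site. Omitting age, sex and BMI, which the component analyses include, may add residual bias of either sign, so the net direction is not determined. The sizes rest on assumed outcome distributions, five strata, and assumed site variation and confounder strength. Confidence is moderate, because the SAP that is to give the adjustment detail is not shown. The sample size, the detectable effect and the RCT analysis are unaffected.

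**What to change.** In the SAP, before data lock:

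1. Include stent use in the logistic score model, and compute every patient's score with stent use set to one common value.
2. Keep site, and add at least age, sex and BMI, to match the component analyses under Secondary outcomes.
3. If small sites call for penalised estimation, leave the stent-use coefficient unpenalised. Shrinking it would hand part of the effect back to site.
4. Optionally, add the remaining pain-model covariates (depression, anxiety, narcotic use, baseline pain interference) in a sensitivity analysis.

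The planned stratified win ratio then proceeds as described. In step 4, correcting both parts gave 0.99–1.03 for a true 1.0 and 1.68–1.79 for a true value of about 1.7. The cost is SAP wording, analysis code and four further model terms (stent use, age, sex, BMI). No new data are needed: all four already appear in the protocol's other observational models.
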